#### Randomisation procedures

Participants will be randomly allocated by telephone to the PRP injection group or the placebo injection group using a randomisation schedule prepared and stored by the National Health and Medical Research Council (NHMRC) Clinical Trial Centre. Randomisation will occur according to a 1:1 allocation ratio in blocks with varying sizes of 6 or 10, stratified according to site (Melbourne or Sydney) and radiographic disease severity (Kellgren and Lawrence grades 2 or 3). At the first treatment appointment, a study nurse will telephone the NHMRC Clinical Trials Centre just before administration of the first injection to reveal the participant’s group allocation.

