### Sample size calculations

Primary outcomes will be the 12-month change in (i) overall average knee pain severity over the last week measured using an 11-point numeric rating scale; and (ii) medial tibial cartilage volume from MRI expressed as a percentage. The minimum clinically important difference to be detected in OA trials is a change in pain of 1.8 units (out of 10) [24]. Using control group data from our 12-month RCT in people with mild to moderate knee OA, we assume a between-participant standard deviation (SD) of change in pain of 2.4 and baseline to 12-month correlation in scores of 0.29 [30]. We wish to find a 40% reduction in the amount of medial tibial cartilage volume loss with PRP. Based on our data [40], slowing the rate of cartilage loss by this amount could delay the need for knee replacement. We anticipate the control group to lose 2.8% (SD 3.5%) of medial tibial cartilage volume in 12-months [30], with a conservative baseline to 12-month correlation in scores of 0.50. These assumptions, together with an analysis of covariance adjusted for baseline scores, indicate that 115 participants per arm will have 80% power to detect a 40% reduction in loss of cartilage volume with a two-sided significance level of 0.05. With this number of participants, we also have > 99% power to detect the minimum clinically important difference in pain. Allowing for 20% loss to follow-up, we will recruit 144 participants per arm - total 288 participants.

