### Statistical analyses

#### Primary analyses

We will conduct an intention-to-treat analysis whereby all participants will be included in the study in the group to which they were randomised. Analysis will be conducted by a biostatistician blinded to treatment group, with two-sided hypothesis tests and *p*-values < 0.05 significant. If the proportion of missing data exceeds 5%, missing outcome data will be imputed using multiple imputation methodology, and sensitivity to the missing at random assumption will be investigated [41]. Changes from baseline will be presented for each group at 2- and 12-month time points using the mean change and 95% confidence intervals. For continuous outcomes (e.g. pain, cartilage volume, physical function), longitudinal analyses will be conducted, with differences in mean change (follow-up minus baseline) compared between the groups using mixed linear regression models with the baseline value, stratifying variables (Kellgren and Lawrence grade and injecting site) and an interaction between month and treatment group as covariates, including random effects for participants [42]. Models including baseline cartilage volume, age, gender, body mass index and cross-sectional area of the medial tibial plateau from MRI [30] will also be fit. Appropriate transformations of outcome measures will be considered if needed to meet statistical assumptions (e.g. linearity, normality and homogeneity of residuals) as assessed using diagnostic plots. Binary outcomes will be compared between groups using risk differences calculated after fitting longitudinal regression models for binary outcomes, adjusted for stratification variables and accounting for clustering of measurements within participants. The other MRI-derived measurements (MOAKS, bone marrow lesion size and cartilage defects) will be compared between groups using appropriate models, adjusting for age, gender, body mass index, and the stratifying variables. The model for cartilage defects will also be adjusted for cross-sectional area of the medial tibial plateau [30]. If appropriate, the effect of PRP on primary outcomes under hypothetical full adherence to assigned treatment will be investigated. The success of blinding will be assessed using the James Blinding Index [43].

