#### Economic analyses

The cost-effectiveness of PRP will be estimated by calculating the incremental average health care cost of those treated and the difference in pain score and health-related quality of life over the 12 months of the trial compared to the placebo group. The comparison will be reported as the incremental cost per unit change in the pain score, the incremental cost per additional quality-adjusted life year, and the net benefit of treatment at 12 months. The quality-adjusted life year will be calculated using the average AQoL-8D value. Net benefits will be calculated using a range of potential money values of a quality-adjusted life year. Costs will include the cost of treatment and associated imaging as well as the downstream medical, pharmaceutical and hospital costs in each arm. Health care utilisation data will be collected by questionnaire. Cost-effectiveness will be calculated using separate generalised linear regression models for costs and outcomes controlling for baseline levels. Predicted costs and outcomes will be used to calculate means for cost-effectiveness ratios and net benefits with bootstrapped 95% confidence intervals. If there is no demonstrated benefit from PRP, we will calculate the incremental average health care cost of those treated. In the secondary economic analysis, the impact on employment and productivity at work will be calculated from data collected by questionnaire.

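### The economic cost and outcome models do not name the two randomisation strata, so their intervals may be slightly wider than needed

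*Protocol article*

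**What the plan says.** Three sections of the protocol article bear on this.

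- *Randomisation procedures*: allocation is 1:1 in blocks of 6 or 10, "stratified according to site (Melbourne or Sydney) and radiographic disease severity (Kellgren and Lawrence grades 2 or 3". That makes four strata.
- *Primary analyses*: continuous outcomes are compared with "mixed linear regression models with the baseline value, stratifying variables (Kellgren and Lawrence grade and injecting site", together with a month-by-treatment interaction and participant random effects. The same section also adjusts the binary outcomes and the other MRI measures for the strata.
- *Economic analyses*: cost-effectiveness is to come from "separate generalised linear regression models for costs and outcomes controlling for baseline levels". Model predictions then give "cost-effectiveness ratios and net benefits with bootstrapped 95% confidence intervals"; the resampling scheme is not described. The effect side of the comparison is "the difference in pain score and health-related quality of life over the 12 months of the trial compared to the placebo group".

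The economic section therefore gives a model type, a covariate set and an interval method, and its covariate set does not mention site or KL grade.

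**The concern.** Stratified blocks force the arms to be nearly balanced on site and KL grade. An analysis that ignores those factors leaves their contribution in the residual, so the standard error describes more chance variation between arms than the design allows. A bootstrap that resamples without regard to stratum has the same fault, because it reintroduces imbalance that the randomisation prevented.

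It is plausible that the strata matter here. The economic section counts downstream medical, pharmaceutical and hospital costs for participants in two cities, and service use may differ between them. KL grade is one of the pre-identified moderators, and the Background cites preliminary evidence that people with milder radiographic disease gain more symptomatic benefit. What is at stake is a modest amount of interval width for incremental cost, QALYs and net benefit, and consistency with the rule that the article follows for its other outcomes.

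**Working it through.** **1. The plan's own figures.** The economic section states none. The sample size inputs, which supply the pain scale used below, do reproduce. The plan says "We anticipate the control group to lose 2.8% (SD 3.5%) of medial tibial cartilage volume in 12-months", with a baseline correlation of 0.50. A 40% reduction is 0.40 × 2.8 = 1.12 points.

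- Unadjusted: n = 2 × [3.5 × (1.960 + 0.842) / 1.12]² = 153.3 per arm.
- With baseline adjustment: 153.3 × (1 − 0.50²) = 114.97, so 115.
- With 20% loss: 115 / 0.80 = 143.75, so 144 per arm and 288 in total.

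This agrees with "115 participants per arm will have 80% power to detect a 40% reduction in loss of cartilage volume with a two-sided significance level of 0.05".

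**2. Pain scale.** From the plan's SD of 2.4 and correlation of 0.29, the residual SD is 2.4 × √(1 − 0.29²) = 2.30. The standard error of the arm difference with 115 per arm is 2.30 × √(2/115) = 0.30 NRS points.

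**3. Interval width by formula.** Let R² be the share of residual variance explained by site and KL grade after baseline adjustment. The documents do not give it; 0% to 20% is assumed here. In a linear model the ratio of interval widths, strata omitted to strata included, is 1/√(1 − R²).

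**4. Simulation.** For each R², 4,000 trials were generated with 230 analysed participants, permuted blocks of 6 or 10 within four equally likely strata, a pain effect of −1.8, and a linear model with and without the strata using model-based standard errors. The Monte Carlo error of a coverage figure is about √(0.95 × 0.05 / 4,000) = 0.3 percentage points.

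| Assumed R² | Width ratio (formula) | Width ratio (simulated) | Coverage of nominal 95% CI, strata omitted | 95th percentile of absolute gap between the two pain estimates |
|---|---|---|---|---|
| 0% | 1.000 | 1.000 | 95.0% | 0.011 |
| 1% | 1.005 | 1.005 | 95.4% | 0.015 |
| 2% | 1.010 | 1.010 | 95.7% | 0.019 |
| 5% | 1.026 | 1.026 | 96.0% | 0.028 |
| 10% | 1.054 | 1.055 | 96.1% | 0.037 |
| 20% | 1.118 | 1.119 | 96.8% | 0.048 |

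**5. Reading the table.** The mean pain effect agrees with and without the strata to within 0.001, at about −1.80. The actual spread of the two estimates is also nearly the same (SD 0.275 and 0.274 at R² = 20%). So omitting the strata hardly changes the estimate; it overstates the uncertainty attached to it. Within one trial the two estimates differ by less than 0.05 NRS points in 95% of runs even at R² = 20%, against a standard error of about 0.30.

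**6. Limits of the check.** Costs were not simulated because the article gives no cost distribution. The planned intervals are bootstrapped from generalised linear models, so the linear ratio is only a guide for them. Balance was imposed on the 230 analysed participants; loss to follow-up after randomisation was not modelled.

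**The case against.** The strongest reply is that this is one paragraph of a condensed article, that the Abstract calls the economic evaluation separate, and that a fuller covariate list may exist elsewhere. The adjustment rules under Primary analyses are not said to govern the economic models, so nothing is contradicted. All of this stands, and it limits the point. A reader might infer that the economic models adjust for baseline levels and nothing else; the text does not say *only*, so that reading goes too far. What remains is that the section does state a covariate set, and that this set lacks the factors the article names for its other outcomes.

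A second reply is that the loss may be nil. That also stands: the documents give no prognostic strength for site or KL grade on cost, pain or AQoL-8D, and baseline adjustment may already absorb much of it. It cannot be said outright that the intervals are too wide.

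A third is that the consequence is small because the Background makes the economic evaluation depend on benefits being found. This holds only in part, since the economic section still plans an incremental cost estimate when no benefit is shown.

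**Conclusion.** A minor point of precision and consistency, and conditional. With an assumed residual R² of 2% to 10%, the economic intervals may be about 1% to 5% wider than needed; at 0% there is no loss. The direction is conservative. Allocation is balanced within strata, so the omission brings no bias, and the primary analysis and sample size are unaffected. The percentages rest on a linear model and an assumed R², and are indicative only for bootstrapped cost-effectiveness ratios and net benefits.

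A reader might also infer that leaving out the strata gives the economic evaluation a pain effect different from the primary result. The check does not support this: the expected effect is unchanged and the single-trial gap is negligible beside the standard error. Any larger gap would come from the model form and the quantity estimated, namely a difference across the 12 months from a separate generalised linear model against a 12-month change from a longitudinal mixed model. Adding the strata would not remove that gap.

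**What to change.** After "separate generalised linear regression models for costs and outcomes controlling for baseline levels", add *and the stratifying variables (KL grade and site)*, so that it applies to both the cost and the outcome models. Add that bootstrap samples are drawn within arm and stratum. If a fuller economic analysis plan already specifies this, it is enough to align the wording.

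The cost is a few words and a few degrees of freedom. Both variables are known for every participant at randomisation, so no data collection changes.

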### Timelines

Ethics approval was obtained from the Human Research Ethics Committee of the University of Melbourne in October 2016. Ethics approval was obtained from the North Sydney Local Health Districts ethics committee in March 2017 and governance approval from the Northern Sydney Local Health Districts Governance office in July 2017. Recruitment commenced in August 2017 and is anticipated to be completed in December 2019. The trial is due for completion in December 2020 when all participants will have completed 12-month follow-up.

## Discussion

Identifying treatments that reduce symptoms and slow disease progression in knee OA is an important OA research objective. Outcomes from this study will provide the first high-quality RCT evidence of the symptomatic and structural benefits of PRP to either support or discourage use of PRP for knee OA. This is important given that several systematic reviews [22, 45, 46] have highlighted the limited number of RCTs that included a placebo control, all previous trials have a moderate to high risk of bias, and none have included structural outcomes. Likewise, current clinical guidelines vary in their recommendation for PRP, with some not including recommendations either for or against PRP given the lack of evidence [47, 48], and others recommending against their use [4]. Findings from the RESTORE trial will, therefore, provide essential information to fill a major evidence gap in the literature and will inform international clinical practice guidelines.

## Abbreviations

AQoL: Assessment of Quality of Life
HREC: Human Research Ethics Committee
ICOAP: Intermittent and Constant Osteoarthritis Pain questionnaire
KOOS: Knee Injury and Osteoarthritis Outcome Score
MOAKS: Magnetic resonance imaging Osteoarthritis Knee Score
MRI: Magnetic resonance imaging
NHMRC: National Health and Medical Research Council
NRS: Numerical rating scale
OA: Osteoarthritis
PASE: Physical Activity Scale for the Elderly
PRP: Platelet-rich plasma
QALYs: Quality Adjusted Life Years
RCT: Randomised controlled trial
WHO HPQ: World Health Organisation Health Performance Questionnaire
